## Abstract

**Background:**

Excess of weight is a serious public health concern in almost all countries, afflicting people of different ages and socioeconomic backgrounds. Studies have indicated the need for developing treatment strategies that intervene directly in the obesogenic environment. This study aims to evaluate the effectiveness of a multi-component and environmental school-based intervention, lasting 16 months, on the recovery of the nutritional status of low-income children and adolescents with overweight/ obesity.

**Methods/study design:**

The study was conducted by the Center for Recovery and Nutritional Education (CREN) in São Paulo, Brazil. Two schools located in poor neighborhoods were selected for the intervention, between March 2016 and June 2017. The participants were all students aged 8 to 12 years from the two participating schools. At the beginning of the intervention, anthropometric measurements were carried out to assess the nutritional status of the students. For convenience, students from one of the schools were considered as the control group, while those from the other school formed the experimental group. The intervention in the experimental group (*n* = 438) consists of the following weekly activities at school: psychological counseling in groups, theoretical/practical nutrition workshops, and supervised physical education classes. In addition, theoretical and practical educational activities are held regularly for parents, teachers, and cooks. Students with excess of weight (≥1 body mass index [BMI] –for-age Z score, *n* = 138) received clinical and nutritional care periodically at the outpatient care at CREN. Students enrolled in the control group (*n* = 353) participated in psychological counseling groups and theoretical/practical nutrition workshops for 6 months held in the school environment to provide motivation to entire classrooms. In the following 10 months, students with excess of weight from the control group (*n* = 125) were invited to attend the routine outpatient care at CREN.

**Discussion:**

This study is the first to assess the effectiveness of a multi-component and environmental school-based intervention for the recovery of low-income, overweight/obese children and adolescents. If positive, the results demonstrate the feasibility for the recovery of excess of weight in populations of similar conditions and age.

**Trial registration:**

Brazilian Registry of Clinical Trials - ReBEC Primary Id Number RBR-9t2jr8. Registration Date: Nov. 30, 2016. Retrospectively registered.

**Protocol version:** 3.

## Background

The World Health Organization (WHO) estimated 155 million or one in 10 school-age (5–17 years old) children worldwide to be either overweight or obese [1, 2]. The prevalence of excess of weight has markedly increased, not only in rich countries, but also in developing countries [3]. It is estimated that by 2025, Latin American countries with large populations, such as Brazil, Argentina, Chile, Peru, and Bolivia, could account for more than 75 million overweight children in the absence of effective intervention [4] .

The Brazilian Family Budget Survey shows that in children the prevalence of overweight and obesity among children is around 36% and 16%, respectively [5]. In adolescence, the prevalence of overweight and obesity is 20.5% and 5.9%, respectively. In large urban centers of the Southeast region, the prevalence of overweight is 38.8%. Among boys aged 10 to 19 years, the prevalence of overweight increased from 3.7% (1974–75) to 21.7% (2008–09). Among girls, the growth of excess weight was from 7.6% to 19.4% in the same age group. Obesity trends increased from 0.4% to 5.9% among boys and from 0.7% to 4% among girls. This situation reflects the nutritional transition scenario observed in Brazil, with a decline in the prevalence of childhood undernutrition and an increase in overweight at alarming levels across all age groups [5].

It is well known that weight gain is related to high consumption of low-nutrient products rich in sugars, fat, and salt (such as snacks and fast foods); routine consumption of sugary drinks; and insufficient physical activity [6–8]. From the nutritional perspective, it is recognized that personal eating preferences, purchasing decisions, and eating behaviors are influenced by price, marketing, availability, and accessibility. In turn, these factors are influenced by policies and regulations for agriculture and trade in food and beverages [9].

Since obesity is a multifactorial disease, effective interventions should have an environmental approach aimed at bringing about behavioral changes that impact on the obesogenic lifestyle [2, 10]. Low-income populations are the most affected, with less access to health care, and therefore, they are more likely to develop comorbidities associated with obesity [2, 5, 9]. Considering that behavioral change requires a sustained commitment by patients and families, motivation is the most important and most challenging aspect of obesity management [10]. A growing number of studies has shown that the motivational aspect is a predictor of success in the treatment of obesity, especially when it involves family members [11, 12].

Many children who have excess weight suffer from significant psychological problems, including anxiety, depression, attention-deficit hyperactivity, bullying, as well as other emotional and eating disorders [13, 14]. In addition, excess weight carries a social stigma that adversely affects children as well as their families [17]. For this reason, environmental interventions that include all children of a classroom, for example, can have better long-term benefits. This approach may facilitate youth leadership towards better health practices and reduce stigmatization of those with excess of weight [15].

Childhood excess of weight is a complex disease. This complexity makes it challenging to design interventions and test different treatment approaches at different settings. Traditionally, most treatments are administered exclusively in healthcare settings and do not offer a multi-component approach encompassing long-term educational and environmental interventions. For this reason, a treatment that includes a school-based intervention can offer a broader approach to changing feeding habits by including motivational groups during school classes, as well as nutrition education groups and supervised physical education classes. In addition, although recent reviews conclude that many interventions can induce weight loss in children and adolescents, effective and sustainable intervention protocols that allow the recovery of childhood excess of weight have yet to be identified [2], especially in low-income settings.

## Methods

### Study design

This is a controlled, prospective trial aimed at investigating the effectiveness of a 16-month, multi-component, and environmental school-based intervention for recovery of poor income overweight/obese students in which subjects are not randomly allocated. This study design was chosen since evidence increasingly has shown that randomized control trials (RTC) are not the most suited models to test the complex and chronic care required to treat children and adolescents with excess weight [15]. Moreover, the present design does not allow randomization of control and experimental groups, since the intervention involves the entire school environment.

### Study population

Two schools were chosen for this study among the three existing schools of the Southeast area of the city of São Paulo, Brazil. The schools have similar teaching schedules, are located in poor neighborhoods, and have students from equivalent socio-economic backgrounds. The selection criterion was their geographical location or proximity to the Center for Recovery and Nutritional Education (CREN), from where the Program is being managed. In all, 1003 children of the defined age group were enrolled in the two schools. After the first analysis, it was verified that 213 children did not meet the inclusion criteria, reducing the number of eligible participants to 791. The study included all the students between 8 to 12 years of age (*n* = 791) enrolled in the two schools. One school was chosen as the experimental group (*n* = 438), and the other was the control group (*n* = 353).

### Sample size calculation

A power analysis was conducted based on the changes in standardized BMI. Assuming an alpha error of 0.05, power of 0.80, and mean difference of the delta (post-intervention vs. baseline measurement) of standardized BMI of 0.12 relative to the control group, with a standard error of 0.30, the estimated number of participants need to be studied per group is 98 (total = 196) [16]. The estimated difference of 0.12 in the standardized BMI was based on previous intervention studies in obese children [17].

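### The 98 per group assumes independent students, but each arm is one school, so the 5% error rate and 80% power do not hold for a programme effect and arm cannot be separated from school

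*Protocol article*

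**What the plan says.** Sample size calculation: the inputs are "Assuming an alpha error of 0.05, power of 0.80", a difference in change "of standardized BMI of 0.12 relative to the control group", and a spread given as "with a standard error of 0.30". The result is that "the estimated number of participants need to be studied per group is 98 (total = 196". The section gives no intraclass correlation, design effect or number of clusters.

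Study population: "Two schools were chosen for this study among the three existing schools" in the area, and "One school was chosen as the experimental group" while the other became the control. The abstract adds that this assignment was made for convenience. Study design says that allocation was not randomized because the intervention covers the whole school. At school, the programme is delivered to classroom groups of about 35.

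Abstract, Discussion: "If positive, the results demonstrate the feasibility for the recovery of excess of weight in populations of similar conditions and age".

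Analysis plan and statistics mentions mixed models and a fixed-effects model adjusted for age, gender, pubertal stage and the difference in group sizes. It names no school or classroom effect. Classroom appears only as a predictor in the imputation model.

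**The concern.** The protocol's own rationale makes the school the unit of intervention, but the sample size counts students as if each had been allocated separately. Children in one school share food, staff, teaching and local events over the 16 months. If those influences shift BMI z-score in one school and not in the other, a student-level test sees a difference between arms and its standard error takes no account of the cause.

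At stake is what a significant result means. The stated error rate and power suggest a test of the programme. What the design delivers is a comparison of two particular schools, one of which had the programme.

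**Working it through.** **Inputs from Sample size calculation:** alpha 0.05 (two-sided reproduces the figure; one-sided gives 78), power 0.80, difference 0.12, spread 0.30. **Excess-weight students:** 138 experimental and 125 control (Outpatient treatment sections). **Schools per arm:** 1. **Assumed, not in the document:** school ICC for change in BMI z-score of 0.005, 0.01 or 0.02.

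**1. The plan's figure.** n = 2 × (1.96 + 0.8416)² × 0.30² / 0.12² = 98.1 per group. Power at 98 is 80.0%. So 98 is the independent-students formula with a design effect of 1.

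**2. The label.** Step 1 uses 0.30 as a standard deviation. If 0.30 were the standard error of the difference, z would be 0.12/0.30 = 0.4 and power about 7%, so 98 could not follow. It is a labelling slip and n does not change.

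**3. Degrees of freedom.** Two schools minus two arms leaves 2 − 2 = 0. The between-school variance cannot be estimated, and arm and school are the same variable. This step needs no ICC.

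**4. Student-level standard error.** At 98 per group: 0.30 × √(2/98) = 0.0429. At 138 versus 125: 0.30 × √(1/138 + 1/125) = 0.0370.

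**5. False positives of a student-level test.** The true variance is larger by DE = 1 + (m − 1) × ICC, with m = 98, or the harmonic mean 2/(1/138 + 1/125) = 131.2. The actual type I error is 2 × [1 − Φ(1.96/√DE)].

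| School ICC | DE, 98 per group | Type I error | DE, 138 vs 125 | Type I error |
|---|---|---|---|---|
| 0 | 1 | 5% | 1 | 5% |
| 0.005 | 1.49 | 11% | 1.65 | 13% |
| 0.01 | 1.97 | 16% | 2.30 | 20% |
| 0.02 | 2.94 | 25% | 3.60 | 30% |

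More students per school make the error rate worse, because DE grows with m.

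**6. Power of the same student-level test.** Φ[(0.12/SE − 1.96)/√DE], with SE from step 4 and the negligible opposite tail added. At 98 per group (0.12/0.0429 = 2.80) this gives 75.5%, 72.6% and 69.1%. At 138 versus 125 (0.12/0.0370 = 3.24) it gives 84%, 80% and 75%, against 90% at ICC 0.

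**7. How much school drift matters.** With no programme effect, the difference in mean change between two schools has standard deviation 0.30 × √(2 × ICC) = 0.030, 0.042 and 0.060. At ICC 0.01 that is about as large as the student-level standard error at 98 per group. An observed difference of exactly 0.12 loses nominal significance if 0.12 − 1.96 × 0.0429 = 0.036 of it is school drift (98 per group), or 0.12 − 1.96 × 0.0370 = 0.047 (138 versus 125).

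**8. Classrooms alone.** Suppose the schools did not differ at all. A class of 35 holds about 35 × 138/438 = 11.0 or 35 × 125/353 = 12.4 excess-weight students. At assumed class ICCs of 0.01, 0.02 and 0.05 the design effects are 1.10–1.11, 1.20–1.23 and 1.50–1.57, and the power at 98 per group of a test that allows for classes is about 76%, 72% and 61–63%.

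**The case against.** **Non-randomization is disclosed and the schools are described as similar.** Both are true. Study design is open about the lack of randomization, and Study population says that the schools match in schedule, poor neighbourhoods and socio-economic background. That supports comparability at the start. It does not make the between-school variance of change zero, and neither statement qualifies the power claim.

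**The outcome is a change from baseline.** This stands and limits the point. Stable differences in level between the schools cancel, so only differential change, or drift between the two measurement rounds, is confounded with arm. A reader might infer that every school difference, including measurement, counts as programme effect. The document does not support that: Data collection describes one measurement procedure and does not suggest that it differed by school.

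**Mixed models may handle the clustering.** They could carry a classroom effect, and the fuller plan that this article condenses may specify one. They cannot separate school from arm when each arm has one school.

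**Power collapses.** A reader might apply the design effect and conclude that power at 98 per group falls to 63%, 51% or 37% at ICCs of 0.005, 0.01 and 0.02. Those figures belong to a test corrected with a known school ICC, which this design cannot run. The student-level test loses far less power (step 6); its fault is the error rate.

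**The abstract claims only feasibility.** In part this stands: the wording stops short of claiming efficacy, and the main Discussion is hedged. The sentence still extends from two schools to other populations, so softening is enough.

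**Conclusion.** The point holds. The arithmetic behind 98 is right for independent students. The error is to present alpha 0.05 and power 0.80 as properties of a design with one school per arm. They hold only if the between-school and between-class variance of BMI z-score change is zero.

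The confounding of arm with school is certain and rests on no assumed figure. The size of the damage does rest on one: under school ICCs of 0.005 to 0.02, a nominal 5% student-level test has a true type I error of about 11% to 25% at 98 per group and 13% to 30% with the actual 138 and 125. These percentages are illustrative.

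It would go too far to say that the study is badly underpowered or needs more students. Enrolment already exceeds 98 per group, and additional students in the same two schools could not remove the confounding.

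**What to change.** 1. In Sample size calculation, change the description of 0.30 from standard error to standard deviation.
2. State there that 98 per group gives 80% power at alpha 0.05 only if students are independent, and drop the claim of 80% power for a programme effect.
3. State in the design and analysis text that arm is fully confounded with school, and that p-values and intervals describe a difference between these two schools. Soften the abstract's concluding sentence to match.
4. Add a sensitivity analysis that reports how large a differential school change would explain the observed effect: how much would remove nominal significance and how much would remove the effect entirely (step 7 shows the form). This should take the place of any table of ICC-corrected power, which would describe a test that cannot be run.

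The cost is a less favourable power statement, some rewording and one sensitivity table. No extra schools or students are needed.

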### Recruitment procedures

Discussions were held with the respective school principals to introduce the project, and after obtaining their formal approval, the intervention began. Parents/guardians were then invited to participate in the study through print communications and telephone calls and asked to attend to a meeting where the objectives and the research protocol were explained. On this occasion, they attended a lecture to raise awareness about the problem of excess weight and its impact on child health. After the lecture, parents and children willing to participate in the program were asked to sign the informed consent forms. The study protocol was approved by the Research Ethics Committee of Human Beings of the Federal University of São Paulo (CAAE: 34,304,714.40000.5505).

### Description of the intervention

The intervention aims at addressing all the possible actors involved in the obesogenic environment, such as family and school. The research team consists of a psychologist, four dietitians, a doctor, and a physical educator.

#### Experimental group

Participants in the experimental group are being enrolled in weekly theoretical/practical group activities at the school throughout the 16-month intervention period. Additionally, students with excess weight receive outpatient care at CREN (Fig. 1).

**Fig. 1 Fig1:**
[figure not shown]
Description of the study and of the Health Multipliers Program Multiplicadores da Saúde (Health Multipliers)

### At school

All students of the 3rd, 4th, and 5th grades participate in the activities in their respective classrooms (Fig. 1). The intervention groups consist of weekly reflective meetings conducted by the psychologist, nutrition education workshops conducted by two dietitians, and physical activities supervised by the specific physical educator of the project in addition to the routine classes of physical activity included in the school curriculum. Further, the research team holds monthly meetings focusing on nutrition education and improved lifestyle for families and students. The following activities are held during these meetings: nutrition workshops, reflective meetings, and physical exercise. Teachers participate in the entire program as collaborators, favoring the youth participation in the proposed activities. Specific monthly meetings are also being conducted for teachers. Moreover, the project team is available to all teachers who wish to receive individualized nutritional care, offering anthropometric and body composition evaluations and nutrition advice.

### Description of the activities at school

**Reflective Meeting**
The reflective meeting is a psycho-educative group activity for seeking solutions and alternatives for common and significant issues of the existence. The theoretical base of this practice is the existential phenomenology and the dialogical group meetings proposed by Paulo Freire [18]. This approach was chosen because the phenomenological exploration in psychology allows a broad understanding of the human experience, with a focus on the meanings, motivations, and decisions for actions. According to *Van Manen & Adams*, it can allow the participants to suddenly see or grasp a human phenomenon in a way that enriches their understanding of everyday life experiences. Such a sudden insight may transform their being and, therefore, their practices [19]. The present protocol employed this methodology as the result of years of experience at CREN regarding treatment in complex environments, such as families facing many difficulties in their relationships. The reflective meeting provides an atmosphere to build new paths for the issues discussed and to explore, by exchanging experiences, better living practices on a daily basis.The meetings occur weekly in groups of about 35 students at a time and last 45 min. Examples of the themes discussed are presented in Table 1. Each theme has been designed to meet the demands identified in their daily life. The psychologist coordinates the group activities in cooperation with another professional aid, who records key information during the sessions. This activity is also being conducted with parents/guardians and teachers.The meetings are designed in accordance with the structure suggested by Szymanski [18], with the following steps: planning, preparatory activity, reflection focused on the demand, and final synthesis.
**Nutritional Education Workshop**
The nutritional education workshop is held in a playful way and includes lectures, videos about childhood obesity and magazine clippings, pictures, posters, slide show, etc. on healthy eating. Examples of the themes discussed are presented in Table 1. The main objectives are to keep students motivated for progressive, healthy changes in eating habits, and nutritional information. This workshop is also being conducted with parents/guardians.The workshops occur weekly in groups of 35 students at a time and last 45 min. The meetings are conducted by two experienced and trained dietitians and follow the same dynamics and methodology of the reflective meetings.
**Supervised Physical Activity**
Once a week, the physical educator conducts physical activities in an adequate space at the school, with groups of about 35 to 40 children for 45 min. The main objective is to encourage the practice of regular physical activity and to teach the students practices that can be replicated at other times in daily life, focusing on youth autonomy and leadership. To favor protagonism, new rules for the games are discussed and created after debate, with the aim of improving collaboration between teams and partners. Tournaments that involve all classes are also being conducted. The descriptions of the activities are presented in Table 1.The meetings with the parents are organized following the reflective meeting methodology and aim to favor the appropriation of physical activity care by all family members, to teach relaxation techniques, and to promote closer ties between parents/guardians and students using the physical activities as a mean. Cooperative games and activities that favor corporal contact between parents/guardians and students are also performed. These activities end with a moment of final reflection to address the apprehension of the meaning of what was accomplished.

**Table 1 Tab1:** Group activities with students and parents/guardians at school

Themes	Objectives
Reflective Meetings With Students	
Establishing bonds of trust	Introduction of the research team to the students Creating intimacy between research team and students Clarification on the school Program “Health Multipliers”
Creating a personal diary to describe life events, perceptions, likings, worries, desires, etc	Creating an instrument that fosters dialog among students, between students/teachers or research team Teaching the students how to use the diary regularly
Is it possible to change?	Discussing how students conceive themselves in that moment and what they would like to change in their lives Discussing about body self-image Discussing about which changes are possible and how to achieve them Considering obstacles that make changes in a difficult life Sharing experiences of students who have managed to change something in their lives, in particular, considering how they overcame obstacles in the classroom Discussing about how it was possible for them to overcome such obstacles
How do I feel? What do I do?	Favoring self-perception of their feelings at any given moment Encouraging self-perception of more recurring feelings in their lives Understanding how their feelings interfere on their day-to-day actions Discussing if anyone in the group has ever experienced a situation in which, because of being under the influence of a strong feeling, has done something he/she regrets Discussing if anyone, by perceiving feelings, was able to avoid some negative situation Discussing about how did it happen.
How to deal with difficulties?	Remembering situations that caused negative feelings Remembering how they reacted to such situations Remembering situations in which the students have actually succeeded in reacting in a satisfactory manner Discussing about how students find the solution and how they can extend this solution to the lives of others
How to have fun in the real world?	Understanding how students usually have fun in daily life Considering the context in which fun happens: with whom, where, when, etc. Remembering situations where they have been able to enjoy without having to use electronic equipment Discussing about how that student found the solution, and how they can extend this solution to the lives of others
Getting to know each other	Understanding what the students usually do together Considering the context where they meet and interact Understanding the barriers to meet friends Remembering situations where they met to have fun Understanding how they can expand social interaction among them
Reflective Meetings Parents/guardians	
How to find time?	Understanding how they reconcile healthy habits and commitments, such as work, home care, children, and so on Understanding if “health” is a priority in their lives Reflecting on the consequences of a sedentary life Understanding if they consider an active life for their children important, and how they encourage them to do so Reflecting on moments in which it was possible to find time within the routine of each one to practice some activity that promotes their own health as well as their children’s
Dialogue, intimacy, and leadership	Understanding how they engage in dialog with their children Understanding if there is freedom of both parties—children and parents—for dialog Promoting dialog between the parties Understanding how they perceive themselves as protagonists of their own life and family life Reflecting on how to improve dialog between the parties and whether anyone in the group has already succeeded at this
Nutrition Workshops Students	
Knowing the food routine of the students	Understanding their eating routine and promoting reflection on how to improve it
Healthy versus unhealthy foods	Identifying food preference Reflecting on concepts of healthy and unhealthy foods
Knowing the ultra-processed food	Discussing the main nutritional differences between natural, minimally processed and ultraprocessed foods by looking at labels and packages of industrialized products Reflecting on the impact of the consumption of these foods on their health
What do I eat?	Comparing the amounts of sugar, fat, and salt of natural and ultra-processed food.
Olympics in Brazil: what do athletes eat?	Reflecting on feeding habits of famous athletes and comparing them with food choices of students
What food is this?	Knowing and identifying natural foods
Cooking workshop: how to prepare tasty and delicious foods in a healthy way	Learning easy recipes for making ice-cream using real fruits in the preparation Awakening interest in developing these recipes at home
Nutrition Workshops Parents/guardians	
Breakfast and quality of life	Developing easy, inexpensive recipes for a breakfast routine Talking about the relationship between eating breakfast, weight gain and the quality of life
The use of milk	Discussing the consumption of milk from birth to the present moment in their children’s life Knowing their preferences and frequency of milk consumption Remembering the milk recipes developed by the family Making together preparations of milk mixed with fruits Sharing the experience of making and tasting the recipes developed Discussing how to improve the family diet routine by milk consumption
Motivation to achieve nutritional goals	Reflect, through the use of motivational sentences, about the difficulties they face to achieve the nutritional goals propose during the reflective meetings Discussing the concepts that each one has about certain food, body composition, and life habits
Physical activity Students	
The importance of physical activity for health	Raising awareness among students about the importance of regular physical activity for health and well-being maintenance
Stretching and relaxation activities	Guidance on stretching and relaxation techniques so students can apply them in everyday life
Folk dance	Constructing a folkloric dance choreography involving students and teachers, to present to parents and communities during a school festivity
Knowing about sports and competitions	Two sports modalities were chosen, rugby and free dance, after discussion with the students. The students then studied the theory of each one of them, familiarized with the rules and applied the knowledge to propose new rules during the training Physical activities involved exercises of strength, aerobics, balance, and resistance, culminating in a sporting tournament
Competition between classes	A competition between classes occurred at the end of the first semester of intervention, counting on the involvement of children from three different classes and their teachers
Physical Activity (Parents/guardians)	
Dialog with parents	Dialog with parents/guardians about the importance of physical activity to the health and well being of their children
Playing with parents	Developing plays to support contact and interaction between parents/guardians and children
Relaxing with parents	Developing exercises of relaxation involving parents/guardians and their children to support the bond between them

